### Recruitment process

Consecutive patients with ABI who follow outpatient rehabilitation at Rijndam Rehabilitation are screened for eligibility based on the inclusion and exclusion criteria by one of their treating therapists. Eligible patients receive an invitation letter from their therapist for the ABI-MOTION study and are asked for their consent to be contacted by the researchers. If they agree, the researcher will contact the patient after a reflection period of 1 week. Prior to inclusion, the participant is asked to provide written informed consent for the study. Therapists and physicians from Rijndam Rehabilitation, sports consultants from SportMEE and other network stakeholders will be recruited by one of the researchers.

### ABI-MOTION intervention

The ABI-MOTION intervention consists of 5 activities (figure 1). The programme starts with outpatient rehabilitation for patients with ABI (1), provided in the rehabilitation centre by a multidisciplinary team which may include a rehabilitation physician, physical therapist, occupational therapist, psychologist and/or movement therapist. In addition, during outpatient rehabilitation a brain education flyer is provided by a physical therapist (2), with information about ABI, PB guidelines and benefits of an active lifestyle. The community-based service will be integrated in outpatient rehabilitation by arranging an introduction of the participant to a sports consultant during outpatient rehabilitation (3). After rehabilitation discharge, patients may receive a maximum of 8 hours of sports consultancy, depending on their needs, which is delivered by the sports consultants of the SportMEE programme (4). There are no eligibility criteria for the SportMEE consultancy programme. About 6 and 12 months after rehabilitation discharge, the patient has follow-up consultations with the rehabilitation physician (5) as part of outpatient rehabilitation care. The control group receives activities 1 and 5. The intervention group receives all 5 activities.

### Implementation of ABI-MOTION intervention

An implementation protocol for the ABI-MOTION intervention was developed prior to the start of the study. This protocol describes relevant stakeholders, expected implementation determinants and corresponding implementation strategies. In addition, potential barriers and facilitators for implementation are described separately as more specific determinants of the implementation process.

Key stakeholders in the implementation process include healthcare professionals from Rijndam Rehabilitation, sports consultants from SportMEE and individuals with ABI. In addition, other sports or exercise organisations in the Rotterdam region, as well as the management teams of both Rijndam Rehabilitation and SportMEE are expected to play a role in the implementation of the ABI-MOTION intervention.

Based on prior discussions with the stakeholders during the preparation phase of the study (unpublished), knowledge, awareness and self-efficacy are expected to be important implementation determinants. Table 1 presents an overview of these determinants with the corresponding implementation strategies according to the taxonomy of behaviour change methods.^28^ Ensuring that all stakeholders have sufficient knowledge on the ABI-MOTION intervention and the benefits of an active lifestyle, through discussion and elaboration and improving awareness and self-efficacy of the stakeholders by raising consciousness and guided practice*,* is expected to contribute to successful implementation of the ABI-MOTION intervention. Table 2 describes examples of more specific determinants for implementation of the ABI-MOTION intervention. These barriers and facilitators are categorised according to six levels of healthcare as described by Grol and Wensing.^29^

**Table 1 T1:** Description of the potential important implementation determinants and corresponding strategies

Determinant	Strategy	Description
Knowledge	Discussion	Researchers engage healthcare professionals in structured discussions about the activities of the ABI-MOTION intervention; healthcare professionals discuss the intervention and the benefits of an active lifestyle with individuals with ABI
	Elaboration	Sports consultants emphasise the importance and benefits of an active lifestyle during their contact with the participant; after rehabilitation discharge, physicians and sports consultants continue to repeat and highlight this in follow-up consultations
Awareness	Consciousness raising	Researchers provide information to healthcare professionals and sport consultants about the ABI-MOTION intervention and its added value to standard rehabilitation care; healthcare professionals and sports consultants raise awareness in individuals with ABI about participating in the ABI-MOTION intervention and the benefits of an active lifestyle during and after rehabilitation
Self-efficacy	Guided practice	Researchers provide feedback on the implementation of the ABI-MOTION intervention to healthcare professionals and sports consultants; individuals with ABI are supported by healthcare professionals and sports consultants with feedback and encouragement to integrate physical activity into daily life in the long term

ABI, acquired brain injury.

**Table 2 T2:** Level of healthcare and related potential barriers and facilitators

Level	Barriers (B) and facilitators (F)
Innovation	B: Feasibility of the integration of SportMEE in Rijndam F: Positive experiences with ABI-MOTION intervention activities
Individual health professional	B: Existing routines of the healthcare professionals F: Interest of healthcare professionals in ABI-MOTION
Patient	B: Lack of knowledge, not aware of advantages of an active lifestyle F: Rehabilitation phase ‘window of opportunity’
Professional interactions	B: Communication between rehabilitation and SportMEE F: One contact person of SportMEE
Organisation	B: Capacity SportMEE, planning of care F: No extra or new care, but combination of existing (after)care
Society	B: Costs of (after)care, limited financial resources F: Experience SportMEE in Rotterdam region (cultural context)

ABI, acquired brain injury.

Prior to the implementation of the ABI-MOTION intervention and during the recruitment period of the control group (ie, phase I), the implementation protocol, including the roles of all stakeholders, will be specified and described in more detail. In addition, all study procedures will be discussed with all stakeholders. After finishing inclusion of the control group, the ABI-MOTION intervention will be implemented and inclusion of the intervention group will start. During this second phase, the implementation protocol will be applied and optimised by verifying the implementation determinants described in tables1  2. The corresponding implementation strategies are also verified and may be updated if needed, according to the five steps of the implementation mapping method: (1) analysis of implementation factors, (2) defining change goals, (3) choosing useful theories and congruent strategies, (4) selecting strategies and (5) practical plan for a tailored implementation strategy.^28 30^

### Data collection

For the process evaluation, participants, healthcare professionals and sport consultants are asked to participate in 1 or 2 focus groups and/or semi-structured interviews in different phases of the study. The focus groups and semi-structured interviews are conducted by 2 researchers according to a predefined topic list. In addition, network meetings will be organised at least once a year, with the researchers and network partners. Furthermore, the researchers will document process outputs throughout the whole study. Focus groups and semi-structured interviews will be recorded and transcribed verbatim. The network meetings will not be recorded, but the discussions will be documented directly afterwards and shared with all stakeholders for their additional input. Outputs from the focus groups, interviews and network meetings will be analysed directly after the meetings and will be used to adjust and optimise the ABI-MOTION intervention and its implementation.

For the explorative effect evaluation, participants are followed up to 1 year after discharge from outpatient rehabilitation and will undergo four measurements; a baseline measurement within the last 4 weeks of outpatient rehabilitation and before the start of the other parts of the ABI-MOTION intervention (T0), and at 3 (T1), 6 (T2) and 12 (T3) months post-rehabilitation discharge. Measurements include physical and cognitive functioning tests at the rehabilitation centre, home measurements including activity monitoring and an electronic diary, and (online) self-report questionnaires sent to the participants by mail or postal mail. The T1 measurement consists of (online) self-report questionnaires only. The T0 measurement aligns with an outpatient rehabilitation visit, and T2 and T3 with standard care follow-up visits at the rehabilitation physician (figure 1). During the visits at the rehabilitation centre (T0, T2 and T3), a trained research assistant conducts the tests, asks general questions and provides information and requirements for the home measurements. To reduce potential burden, participants are given flexibility to complete the questionnaires at their own pace, including the option to pause and resume at a later time. Since implementation outcomes are the primary focus, participants who are unable to complete the questionnaires independently (eg, due to aphasia) are not required to do so. Support of proxies in completing the questionnaires is allowed; however, proxies are asked not to complete the questionnaires on behalf of participants.

## Evaluation

The evaluation of the ABI-MOTION intervention will be conducted using the RE-AIM framework, which provides a comprehensive structure for assessing both the implementation process and effects of the ABI-MOTION intervention. Table 3 presents a description of the dimensions of the RE-AIM framework and corresponding evaluation outcomes.

**Table 3 T3:** The RE-AIM framework and corresponding evaluation outcomes for the ABI-MOTION intervention

Dimension	Subtheme	Main question	Evaluation outcomes
Reach	Recruitment	Did the intervention reach the intended population?	Number of patients with ABI in outpatient rehabilitation; potential participants; invited, included and excluded participants and reasons for non-inclusion
Effectiveness	Outcomes Costs	What are the effects and the costs of the intervention?	See table 4 for all effect outcomes
Adoption	Context Acceptability Feasibility	Which contextual factors have influenced the implementation and to what extent was the ABI-MOTION intervention perceived as acceptable and feasible by the stakeholders?	Contextual factors, acceptability, feasibility and barriers and facilitators for implementation of all stakeholders.
Implementation	Fidelity Dose delivered Dose received	To what extent was the ABI-MOTION intervention implemented as intended?	Protocol adherence for the new activities of the ABI-MOTION intervention
Maintenance	Applicability	Can ABI-MOTION be sustained and integrated into routine care in the Rotterdam region?	Care Process Self-Evaluation Tool questionnaire for healthcare professionals; barriers and facilitators for sustained delivery of the ABI-MOTION intervention, especially after the inclusion and research phase

ABI, acquired brain injury; RE-AIM, Reach, Effectiveness, Adoption, Implementation and Maintenance.

**Table 4 T4:** Outcomes effect evaluation

	During outpatient rehabilitation	T0: baseline before discharge and start of intervention	T1: 3 months post discharge	T2: 6 months post discharge	T3: 12 months post discharge
Physical and cognitive functioning test at the rehabilitation centre					
1 min sit-to-stand test		X		X	X
10 m walk test		X		X	X
Handgrip strength: JAMAR dynamometer		X		X	X
Cognitive functioning: MoCA		X		X	X
Aphasia: ABC		X		X	X
Functional ambulation categories		X		X	X
Anthropometry		X		X	X

Self-report questionnaires: online (or postal) at home					
Participant characteristics		X	X	X	X
Clinical characteristics		EPR	X	X	X
General questions		X	X	X	X
Physical activity: IPAQ		X	X	X	X
Physical fitness: IFIS		X	X	X	X
Anxiety/depression: HADS		X	X	X	X
Cognitive complaints: CFQ		X	X	X	X
Quality of life: EQ-5D-5L, SF-36		X	X	X	X
Coping: CISS-SF		X	X	X	X
Fatigue: CIS		X	X	X	X
Participation: USER-P		X	X	X	X
Healthcare use: iMCQ		X	X	X	X
Return to work: iPCQ		X	X	X	X

Home measurements					
Physical behaviour: GENEActiv		X		X	X
Intention/motivation: electronic diary		X		X	X

Focus groups and Interviews					
BCW: capability, opportunity, motivation	X	X	X	X	X

ABC, Aphasia Bedside Check; BCW, Behavior Change Wheel; CFQ, Cognitive Failure Questionnaire; CIS, Checklist Individual Strength; CISS-SF, Coping Inventory for Stressful Situations – Short Form; EPR, Electronic Patient Record; EQ-5D, EuroQoL-5D; HADS, Hospital Anxiety and Depression Scale; IFIS, International FItness Scale; iMCQ, iMTA Medical Consumption Questionnaire; IPAQ, International Physical Activity Questionnaire; iPCQ, iMTA Productivity Cost Questionnaire; MoCA, Montreal Cognitive Assessment; SF-36, Short Form Health Survey-36; USER-P, Utrecht Scale for Evaluation of Rehabilitation – Participation; X, study measurement.

### Evaluation of implementation process

The evaluation of the implementation process addresses the RE-AIM dimensions: reach, adoption, implementation and maintenance (table 3). These dimensions will be explored through both quantitative and qualitative methods, including documentation, registration, focus groups, semi-structured interviews and network meetings.

Reach will be assessed by quantifying the extent to which the intervention successfully reached the target population (ie, individuals with ABI who follow outpatient rehabilitation). This will be expressed in the total number of patients in outpatient rehabilitation, the number of potential participants identified and those invited, included and excluded from the study. In addition, reasons for non-inclusion will be systematically documented to gain insight into recruitment barriers and representativeness of the study population.

Regarding adoption, the focus will be on the contextual factors that influence the uptake of the intervention, as well as the perceived acceptability and feasibility among all stakeholders. In assessing these aspects, the focus will be on whether the ABI-MOTION aligns with existing care processes, adoption of ABI-MOTION at the organisational level and stakeholder experiences throughout the process of optimising the ABI-MOTION intervention.

The implementation dimension will be expressed in the extent to which the ABI-MOTION protocol was adhered to in practice. This includes measures of dose delivered and dose received, for example, number of introductions to sports consultant during outpatient rehabilitation. These kinds of protocol adherence and deviation measures will be documented and described.

Finally, maintenance will be evaluated using the Care Process Self-Evaluation Tool (CPSET)^31^ filled in by healthcare professionals. In addition, barriers and facilitators for sustained delivery of the ABI-MOTION intervention after the inclusion period and research phase will be explored.

### Evaluation of intervention effects

The effect evaluation focuses on the effectiveness dimension of the RE-AIM framework, by exploring the effects of the ABI-MOTION intervention on several outcomes and associated costs. An overview of all outcomes for the effect evaluation is provided in table 4. The focus is on objectively assessed PB and HR-QoL. PB will be assessed for 7 consecutive days with the GENEActiv (Activinsights, Kimbolton, England), which is a validated wrist-worn accelerometer.^32^ PB will be expressed in PA and SB, including total minutes of PA, light PA, moderate to vigorous PA, SB and sleep per day. HR-QoL will be assessed with the EQ-5D-5L^33^ questionnaire and the SF-36.^34 35^ The EQ-5D-5L consists of the 5-item EQ-5D index (mobility, self-care, usual activities, pain/discomfort and anxiety/depression) and a visual analogue scale.^33^ The SF-36 questionnaire assesses limitations in functioning and entails 8 subdomains, which can be combined into a physical and a mental component score.^34 35^

Other outcome measures include the physical and cognitive functioning tests, the self-report questionnaires, the outcomes of the questions of the electronic diary and the patient and clinical characteristics (table 4). The physical functioning tests include the 1 min sit-to-stand test,^36^ 10 m walk test^37^ and hand grip strength test (JAMAR, Lafayette Instrument Company, Lafayette, Indiana, USA),^38^ which are conducted as a measure of aerobic capacity, walking speed and overall muscle strength, respectively. Cognitive functioning is measured with the Montreal Cognitive Assessment^39^ and aphasia, if indicated, with the Aphasia Bedside Check test.^40^ The level of independence in walking is assessed with the Functional Ambulation Categories.^41^ Anthropometry includes length and weight, waist circumference and arm circumference; length and weight, which will be used to calculate body mass index (BMI).

Participant characteristics that will be collected include age, sex, education, living situation (alone/with others), pre-injury work status (paid/unpaid/retired), migration background, BMI, smoking, pre-injury activity status using the Saltin-Grimby Physical Activity Level Scale^42^ and socio-economic status (based on postal code). Clinical characteristics will be collected from the electronic patient file and/or the participant will be asked. Characteristics include type of brain injury (eg, traumatic, stroke), time after injury, time between hospital discharge and start of rehabilitation, type of ABI treatment (eg, surgical, endovascular, conservative and pharmaceutical), length of stay in hospital, intensive care (yes/no), duration of inpatient and outpatient rehabilitation, complications, comorbidities (eg, obesity, cardiovascular disease, pulmonary disease, diabetes and other), and smoking, alcohol and/or drugs use.

Validated self-report questionnaires are used to assess, PA (International Physical Activity Questionnaire),^43^ physical fitness (International FItness Scale),^44^ symptoms of anxiety and depression (Hospital Anxiety and Depression Scale),^45^ cognitive complaints (Cognitive Failure Questionnaire),^46^ coping (Coping Inventory for Stressful Situations – Short Form),^47^ fatigue (Checklist Individual Strength),^48^ participation (Utrecht Scale for Evaluation of Rehabilitation – Participation),^49^ healthcare use (Institute for Medical Technology Assessment (iMTA) Medical Consumption Questionnaire (iMCQ))^50^ and return to work (iMTA Productivity Cost Questionnaire (iPCQ)).^51^ Data from the iMCQ and iPCQ questionnaires will be used to conduct a descriptive cost analysis focusing on healthcare use and productivity losses. Questions on the electronic diary refer to sleep quality, and intention and motivation for being physically active.

The effects of the ABI-MOTION intervention in terms of incorporating and maintaining an active lifestyle and behaviour change will also be evaluated through focus groups and semi-structured interviews, using the Behavior Change Wheel (BCW)^52 53^ as framework and focusing on the three main components of the BCW, capability, opportunity and motivation.

### Statistical and qualitative analyses

Descriptive statistics will be used to summarise the documented numbers related to the evaluation of the implementation process and the outcomes of the effect evaluation. Means and SD will be calculated for variables on an interval scale, and medians and IQRs for ordinal variables and if variables are not normally distributed. Proportions will be calculated for nominal variables. ATLAS.ti software (V.24, ATLAS.ti Scientific Software Development GmbH, Berlin, Germany) will be used to analyse and interpret the qualitative data of the focus groups and network meetings. The dimensions and subthemes of the RE-AIM framework, and the BCW, will be used to thematically identify and describe the themes that are discussed.

The changes over time (T0–T3) of the effect outcomes will be analysed with Generalised Estimating Equations (GEE) models for repeated measurements on an intention-to-treat basis using SPSS (V.32, IBM SPSS Statistics, New York, USA). This method takes all observations into account, even if some outcomes are missing, assuming that these data are missing at random. Each parameter at each time point will be included as the dependent variable in separate GEE models. Independent variables that will be added to each model include measurement time (T0, T1, T2 and T3), group (intervention vs control), and the interaction between time and group. In post-hoc analyses, differences between the intervention and control group at each time point will be analysed. If differences in participant or clinical characteristics between the control and intervention group are present, the models will be adjusted for patient characteristics (eg, age, sex and living status) or clinical characteristics (eg, type of injury, type of treatment and comorbidity). Maximal number of covariates in the model will be based on the number of participants in both groups. Potential differences in participant and clinical characteristics between the control group and intervention group will be calculated using independent t-tests for normally distributed interval scale variables, the Mann-Whitney U test for non-normally distributed interval scale variables, and the χ^2^ test for categorical variables. Interim analyses will be performed when all patients from the control group or intervention group have finished the baseline, 3 and/or 6 months follow-up visits.

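### The normality-based summary rule has no exception for costs, so the descriptive cost analysis would, on its ordinary reading, report medians that do not answer the plan's own cost question

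*Protocol article*

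**What the plan says.** All references are to the Protocol article.

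- **Scope of the summary rule.** The section Statistical and qualitative analyses opens by setting what the rule covers: "Descriptive statistics will be used to summarise the documented numbers related to the evaluation of the implementation process and the outcomes of the effect evaluation".
- **The rule itself** (same section): "Means and SD will be calculated for variables on an interval scale", followed by "medians and IQRs for ordinal variables and if variables are not normally distributed". No variable is exempted.
- **Costs are part of the effect evaluation.** Evaluation of intervention effects describes that evaluation as proceeding "by exploring the effects of the ABI-MOTION intervention on several outcomes and associated costs". In Table 3 the main question under Effectiveness is "What are the effects and the costs of the intervention". Table 4 lists the iMCQ (healthcare use) and iPCQ (return to work) at T0 to T3.
- **Type of cost analysis** (Evaluation of intervention effects): "Data from the iMCQ and iPCQ questionnaires will be used to conduct a descriptive cost analysis focusing on healthcare use and productivity losses".
- **Employment mix** (same section): the participant characteristics include "pre-injury work status (paid/unpaid/retired" as categories, without proportions.
- **Group sizes** (Power analysis): 15 control and 45 intervention participants.

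The article does not say that mean costs will be reported, and it gives no expected cost distribution.

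**The concern.** Asking what an intervention costs is asking for cost per patient or total cost. Both follow from the arithmetic mean: the mean times the number of participants is the total, and mean healthcare cost plus mean productivity cost is mean combined cost. Medians have neither property, and a median does not register how large the highest costs are.

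The rule drops the mean when a variable is not normal. Costs and volumes of care cannot be negative, are usually skewed to the right, and often include zeros. The article also anticipates participants who were unpaid or retired before injury, for whom a paid-work loss may not arise. The rule is therefore likely to remove the mean for the variables where the mean is the quantity wanted.

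At stake is whether the cost part of the Effectiveness question gets a usable answer. No primary result is affected.

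**Working it through.** The article states no cost figure, so there is nothing to reproduce. The check has two parts.

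**1. Does the rule reach costs?**

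- The summary rule covers the outcomes of the effect evaluation.
- Costs are placed in that evaluation by its introductory sentence, by Table 3 and by the two cost questionnaires in Table 4.
- The cost analysis is called descriptive, and the summary rule is the only descriptive rule for quantitative data in the article.
- The same section splits the baseline tests in parallel (t-test if normal, Mann-Whitney if not). This supports reading the median as a replacement for the mean.

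So the rule reaches costs on its ordinary reading.

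**2. What would a median show?**

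Group sizes are from the article. Every cost input below is an assumption.

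*(a) Median as a share of the mean.* For a lognormal cost with coefficient of variation CV, median/mean = 1/√(1 + CV²).

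- CV 1.0: 1/√2 = 0.71
- CV 1.5: 1/√3.25 = 0.55
- CV 2.0: 1/√5 = 0.45

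*(b) Chance that both productivity medians are 0.* Let p be the share of participants with any loss, the same in both groups. With 15 participants the sample median is 0 when at most 7 have a loss; with 45, when at most 22 do. The groups are independent, so

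P(both medians 0) = P(Bin(15, p) ≤ 7) × P(Bin(45, p) ≤ 22).

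| p (assumed) | n = 15 | n = 45 | Both 0 |
|---|---|---|---|
| 35% | 0.887 | 0.981 | 0.87 |
| 50% | 0.500 | 0.500 | 0.25 |
| 60% | 0.213 | 0.087 | 0.02 |
| 70% | 0.050 | 0.002 | below 0.001 |

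The shares may also differ between groups. With 40% in the control group and 25% in the intervention group, and a mean of 8,000 among those with a loss, mean loss is 0.40 × 8,000 = 3,200 against 0.25 × 8,000 = 2,000. Both medians are still 0 with probability 0.787 × 1.000 = 0.79.

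*(c) Can median and mean differ in direction?* Suppose readmissions costing 15,000 fall from 15% (control) to 5% (intervention), while mean routine care rises from 2,000 to 2,300. Mean cost falls from 2,000 + 0.15 × 15,000 = 4,250 to 2,300 + 0.05 × 15,000 = 3,050. The population medians depend on the spread of routine (lognormal) cost:

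| CV of routine cost (assumed) | Control median | Intervention median | Direction against the mean |
|---|---|---|---|
| 0.7 | about 1,890 | about 1,960 | opposite |
| 1.0 | about 1,700 | about 1,720 | opposite, but almost no difference |
| 1.5 | about 1,410 | about 1,370 | same |

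A second set of assumptions gives the same mixed picture. Take lognormal healthcare cost with an intervention median of 1,900 and log-SD 0.8 (mean 2,617), and a control median of 1,500.

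- Control log-SD 1.0: the control mean is 2,473, so mean and median agree in direction.
- Control log-SD 1.3: the control mean is 3,492, so the mean difference is 2,617 − 3,492 = −875. The sample median difference has the opposite sign in 70% of 20,000 simulated studies of 15 against 45.

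A reversal is therefore possible, but how often it would happen cannot be fixed from the article.

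**The case against.** **The summary sentence is a general convention.** It does not mention costs, and an article may leave cost detail to the full protocol or analysis plan. It could also be stretched to mean that medians are given in addition to means. This stands in part: replacement is the ordinary reading, not the only one. But the rule is stated positively and its scope includes costs, so the point concerns what is written, not missing detail.

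**GEE might supply the means.** The iMCQ and iPCQ are in Table 4, and the GEE sentence covers the effect outcomes. With the usual links GEE compares means. This too stands in part: a reader may infer that the median rule alone must produce the cost result, and the article does not settle that. It labels the cost analysis descriptive, so GEE does not clearly cover it either.

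**The size is unknown.** This stands. A reader might infer that productivity results would read 0 in both groups whatever the truth. The table above contradicts that: the probability falls from 0.87 to 0.02 as the assumed share with a loss rises from 35% to 60%. Work status is listed only as categories, with no proportions. A reader might likewise infer that medians will point the wrong way. The reversal nearly vanishes at a CV of 1.0 and is gone at 1.5.

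**The stakes are low.** This stands. Implementation outcomes are primary, the effect evaluation is exploratory by the article's own account (Limitations), and no cost-effectiveness ratio, budget estimate or cost hypothesis is described.

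**Conclusion.** The point holds as a minor one. On its ordinary reading, the stated rule summarises non-normal costs by median and IQR, and no exception is made for a cost analysis that belongs to the effect evaluation. Whenever costs are skewed, a median does not give per-patient or total cost and does not add across components. That part needs only skewness, which is expected here but not documented.

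The numerical size rests on assumed distributions. The median might be 45% to 71% of the mean for lognormal costs with CV 2.0 to 1.0. Both productivity medians might be 0 with probability from 0.87 to 0.02 for loss shares of 35% to 60%. A change of direction against the mean is a possibility, with no rate that the article can support. Nothing here affects the primary outcome or the sample size.

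**What to change.** Add one sentence to Statistical and qualitative analyses that exempts healthcare use and productivity costs, and the volumes behind them, from the normality rule. Report the arithmetic mean per participant in each group and the mean difference, with bootstrap intervals, whatever the distribution. Give the median, IQR and percentage with zero as a supplement. State in the same place whether the GEE models are meant to include cost outcomes.

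This needs no new data and no change to design or sample size, only a short bootstrap on data already being collected. The intervals will be wide with 15 controls, which fairly shows how much the study can say about costs.
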